## Abstract

**Background:**

Common disease risk clusters in families due to shared genetics, exposure to environmental risk factors, and because many health behaviours are established and maintained in family environments. This randomised controlled trial will test whether the provision of a family health history (FHH) risk assessment tool increases intentions and engagement in health behaviors. Message distribution and collective behavior change within family networks will be mapped using social network analysis. The relative intervention impact will be compared between families from different ethnic backgrounds.

**Methods:**

One hundred and fifty mothers (50 Anglo-Australian, 50 Italian-Australian, 50 Vietnamese-Australian) will be recruited, with four or more other family members across three generations, including a child (aged 10–18 years). Each family is randomly assigned to intervention or control. At baseline and 6-month follow-up, all participants complete surveys to assess dietary and physical activity intentions and behaviors, attitudes towards food, and perceived disease risk. Intervention families receive a visual pedigree detailing their FHH of diabetes, heart disease, breast and bowel cancer, a health education workbook to ascertain members’ disease risk (i.e. average or above average risk), and screening and primary prevention recommendations. After completion of follow-up assessments, controls will receive their pedigree and workbook. The primary hypothesis is that attitudes and lifestyle behaviors will improve more within families exposed to FHH feedback, although the extent of this improvement may vary between families from different ethnic backgrounds. Additionally, the extent of improvement in the treatment group will be moderated by the level of family disease risk, with above-average risk leading to greater improvement. A secondary aim will explore different family members’ roles in message distribution and collective responses to risk using social network approaches and to compare network functioning between families with different ethnic backgrounds.

**Discussion:**

Results will guide future health promotion programs aimed at improving lifestyle factors. This research will assess whether FHH can motivate families to adopt family-level strategies to support health promoting behaviors. Secondary analyses aim to identify change agents within the family who are particularly effective in shifting normative behaviors.

**Trial registration:**

Australian New Zealand Clinical Trials Registry ACTRN12613001033730. Retrospectively registered: 17 September, 2013.

## Background

Lifestyle-related diseases including heart disease, stroke, diabetes, obesity, metabolic syndrome, chronic obstructive pulmonary disease, and some types of cancer are endemic in many developed countries. These diseases share some or all of four behavioral risk factors; an unhealthy diet, physical inactivity, alcohol consumption, and smoking. The United Nations describes these as “Western diseases” or “diseases of affluence” [1]. The health burden in Australia mirrors this finding, with data suggesting that one third of the nation’s disease burden is linked to poor lifestyle choices [2]. These diseases are etiologically complex. They arise from genetic factors and environments that promote the normalisation of unhealthy food consumption through exploiting human vulnerabilities, be these biological, psychological, social or economic [3–5].

To date, health interventions and policy to reduce lifestyle-related disease have largely adopted behavior change strategies that focus on the individual. However, focusing on families rather than individuals may be a more effective strategy for disease prevention because family members share genetic risk, they are typically exposed to similar environmental risk factors, and health-compromising behaviors tend to cluster within families. Indeed, there is evidence that both food choice [6] and eating behavior [7] show strong consistency in families, even across generations. This highlights dietary practices as an avenue for family-based interventions designed to modify disease risk [8]. Similarly, physical activity is also shown to aggregate within families again highlighting the family context as potentially important for behavior change [9, 10]. In addition, effective use of family health histories (FHHs) as part of family-based disease prevention efforts is a promising mechanism for motivating collective health behavior change. Family health histories capture the complex interactions between shared genetic, lifestyle and environmental factors, and so are ideally suited to informing family-based disease prevention [11]. The potential utility and acceptability of FHH are supported by data from the US Center for Disease Control which, in 2004, reported that the vast majority of the US population (more than 96 %) considered that knowledge of family health history was important to their personal health [12]. This study is concerned with assessing the impact of the provision of families’ personalised FHHs on intentions to modify diet, physical activity and other lifestyle behaviours, and subsequent behaviour, in families with different ethnic backgrounds.

### Family health history assessments to promote disease risk-reducing behaviors

The U.S. Surgeon General and Centers for Disease Control and Prevention (CDC) have instigated FHH initiatives to provide web-based tools designed to encourage individuals to map their family’s history of heritable chronic diseases [13]. To accelerate the use and impact of FHH tools, initiatives have sought to promote behaviors to reduce disease risk directly. These FHH assessment programs typically engage individuals and involve the analysis of information on family morbidity from heritable diseases; feedback on individuals’ disease risk based on FHH trees; and behavioral strategies for risk modification [13–16] “Families SHARE” is one such tool with demonstrated efficacy [17].

Research suggests that individuals provided with a FHH-based risk assessment can make significant improvements to their lifestyle, particularly when provided with individually tailored behavior change information aimed at modifying their disease risk [18]. For example, Sato Ashida, Wilkinson and Koehly [19] completed a longitudinal FHH intervention with Mexican American families and found that participants who received messages of family disease risk (based on a FHH) reported a higher motivation to increase their intake of fruit and vegetables. Further, parents may be particularly motivated to improve their own and their child’s health in response to family risk information. Indeed, FHH-based risk information spurred parent-child encouragement of physical activity, which in turn was associated with parents and children co-engaging in physical activity in the study of Mexican American families [20]. Research by this team has also found that family members with disease experience play a vital role in disseminating information and encouraging or advocating health behaviors in the family, highlighting the potential to harness existing relational processes of communication or influence to improve dietary, physical activity, and other health behaviors within family systems [21].

*Families SHARE*, which will be used in this project, is a FHH tool designed to facilitate understanding of the role of FHH in disease risk by the public [17]. The Families SHARE workbook consists of 1) a personalized pedigree representing family morbidity from specific diseases (including diabetes, heart disease, and cancer), 2) an algorithm for computing a risk assessment based on the family pedigree, and 3) behavioral strategies for risk modification. A recent evaluation of the workbook found that users reported significant increases in intentions to improve dietary behaviour following use of the workbook, suggesting that Families SHARE may be successful in shifting dietary behaviors within the home. In addition, users who were mothers of young children, were able to apply the algorithm to assess their own and other family members’ risk. Feedback indicated a desired focus on their child’s risk, with the suggestion that such a focus would improve parent motivation to shift towards more healthful norms within the home. Taken together, these results suggest that Families SHARE may be a particularly useful tool within a family-based intervention that leverages parent protection motivations geared towards children.

As such, provision of FHH information within a family-centered feedback process may initiate communal coping. A communal coping response involves family members communicating about a health threat (i.e., family risk of disease), developing a shared appraisal of that threat, and engaging in cooperative action to address the threat [22–24]. This would result in an activation and shift in communication, influence, and support among family members, which can heighten awareness of family disease risk and facilitate the adoption of risk reducing behaviors. Despite the promise of FHH initiatives for motivating risk reducing health behaviors within families, there remain two critical gaps in these translation efforts: a lack of research that (1) adapts and evaluates these tools for diverse populations, who have varied family structures and family social dynamics; and (2) explicitly accounts for family systems and their role in the success of FHH interventions. These gaps can be addressed through a cluster randomised controlled trial that provides FHH-based risk information, such as Families SHARE, to diverse, multigenerational families. The extent to which families are impacted is likely to be dependent on actual risk level, habitual behaviors, and cultural traditions with regard to food and lifestyle. Further, research that maps the interpersonal mechanisms that comprise communal coping as potential process variables is limited. Thus, capturing the network of communication and influence relationships among family members will allow us to understand how diverse family structures and systems moderate or mediate intervention effects.

### Transmission of disease risk and related behaviors: the role of family and culture

To a large extent, family health environments are shaped by parents’ beliefs, attitudes, and behaviors, education, and ethnic/cultural backgrounds and norms [25]. Together these factors may create family environments that are more or less promoting of disease risk. Interventions that increase motivation within the family to adopt and maintain healthy behaviors may, in the long term, reduce the prevalence of lifestyle related diseases.

The intergenerational and social ‘transmission’ of lifestyle diseases such as obesity [26], and associated health-risk behaviors emphasize the importance of social processes within families - i.e., family social networks dynamics - and family culture, in reinforcing or changing health behaviors. For example, Christakis and Fowler [26] highlighted the link between interpersonal relationships (i.e., “social ties”) and weight in a large community social network (N = 12,067), with evidence of similarities in weight status among siblings, spouses and friends over time. Subsequent research suggests that similarities in weight status (and potentially other related health outcomes) among socially connected individuals are in part due to social networks directly influencing individual health behaviors (including eating [27–29] and physical activity [30, 31]), and indirectly influencing these behaviours by shaping weight norms [32, 33]. Traditional social psychological research has established that social influence on eating and activity can occur through a variety of interpersonal and group processes including modelling behavior, normative influence, ‘mindless imitation’ and social facilitation.

The impact of social influence on health behaviors is likely to be especially prominent in families, particularly where children still live at home with their parents. There is a strong interplay between parents’ health behaviors and associated health outcomes (i.e., overweight), and children’s health trajectories [34, 35]. For example, the links in dietary behaviors among family members are especially strong. Parents appear to play a particularly important role in the establishment of dietary behavior in children that endures into adulthood [36]. Prichard, Hodder, Hutchinson and Wilson [37] confirmed a strong association between adult daughters’ dietary intake of energy-dense snack foods and vegetables and their perceptions of their mothers’ intake of these same foods with observed correlations of .81 and .52, respectively. These correlations are not entirely due to the number of meals shared, particularly with regards to daughters’ intake of energy dense foods. Data collected on eating behaviors (i.e., engagement in Restrained Eating, External Eating and Emotional Eating) also highlighted strong mother-daughter similarity with correlations between mother and daughter of .33, .52 and .62 respectively for the three behaviors.

There is also evidence of a link between the broader family environment and eating behaviors. Energy dense food consumption and healthy food choices are positively correlated among family members, both across and within generations. For example, fat intake has been found to correlate between parents, mother and child, and father and child [6]. However, family influence on food is also complex, and has been found to differ based on the closeness of the family tie, as well as by family role or position (e.g., child, parent or grandparent), and may also differ across ethnic groups [38].

Ethnicity and associated cultural practices also have an important influence on eating behaviors and health outcomes for families. In Australia, patterns of lifestyle diseases such as obesity in children can be linked to the sub-continental origins of the parents [39]. Italian-Australians have been found to have a higher incidence of overweight than the population, whereas the rate amongst Vietnamese-Australians is lower [40]. Moreover, cancers linked to dietary and other lifestyle choices occur at a significantly higher incidence among some immigrant groups than is found in their country of origin, suggesting that the adoption of Australian normative behavior may be causally associated with this outcome [41]. Identifying how the transmission of eating practices differs across these ethnic groups may allow us to identify influence processes that are protective of, or promote lifestyle-related disease.

Bidirectional, intergenerational influences on eating habits have been documented in families of diverse ethnic backgrounds [25], with children potentially playing an important role in the adoption of ‘new’ behaviors [20, 42]. It is also clear that other family members fulfil powerful roles: mothers in virtually all cultures play a critical role through primacy in meal preparation, whereas grandparents have been found to significantly influence their grandchildren’s diets in some cultures [4]. Families of different social and ethnic backgrounds may differ in their interpretation of food and health information [43], which is likely to impact the salience and meaning of diet in the family. How this impacts understanding and communication of food and health issues in families will be examined in the proposed study.

### The proposed study: using families SHARE to promote healthy eating and other disease risk-reducing behaviors in families with diverse ethnic backgrounds

The literature reviewed above suggests that an intervention providing families with a FHH-based risk assessment focused on lifestyle linked-diseases in conjunction with recommendations towards risk-reducing health behaviors may serve as a motivation for behavior change within families. The Families SHARE workbook provides both a risk algorithm that can be applied to multiple family members as well as lifestyle and screening recommendations focused on disease prevention and early detection. It is hypothesized that provision of the Families SHARE workbook will activate family social network processes which in turn will influence and support the adoption of the promoted health behaviors.

The extent to which families are impacted by such a tool is likely to depend on actual disease risk level, habitual behaviors, communal responses within families, and food and meal traditions associated with ethnic background. Psychosocial variables likely to influence responsiveness to information about familial disease risk and responses on these variables, in turn, may be moderated by age, gender, education and ethnic background. These include differences in social and cultural capital [44, 45], optimism [46] and health locus of control [47]. Each of these variables has a demonstrated relationship to participation in health-related behaviors, self-reported health, or morbidity and mortality and may serve to impact responsiveness to interventions designed to provide motivation to improve lifestyle choices.

Notwithstanding the potential influence of individual difference variables, the proposed study will focus on the family cluster as the primary unit of observation. The primary aim is to discern the impact of inter and intragenerational influence on family food intentions and choices following exposure to a self-generated pedigree of family disease risk. Given past research, which has highlighted ethnic group differences in food intake and meal-time behaviour, this factor will be considered as a potential possible moderator of the impact of exposure to Families SHARE.

The remaining text describes the protocol for a randomised controlled trial of Families SHARE among multigenerational families of diverse ethnic backgrounds in Australia.

## Methods/design

### Study aims

The main aim of the study is to test whether the provision of a FHH risk assessment workbook, Families SHARE, for families to use to identify their familial chronic disease risk and as an algorithm for them to identify the individual risk of any specific family member impacts intention to change diet and actual diet. The potential moderating impact of ethnic background will be considered. A secondary aim is to examine how the intervention alters relationships within family social networks, including the diffusion of messages about disease risk, and the activation of networks that influence and support behaviors, to understand the role family systems play in moderating behaviour change and to understand if the manner in which information provided by the FHH influences diffusion within the networks.

### Study design

This study is a cluster, randomised controlled trial where mothers from Anglo-Australian, Italian-Australian and Vietnamese-Australian ethnic background will be randomly assigned to an intervention (provision of Families SHARE) or control condition (received nothing during the study). The study is longitudinal, with six months elapsing between the completion of baseline and the commencement of the follow-up. For those in the experimental condition, the Families SHARE workbook along with personalized pedigree (i.e., intervention) will be mailed to participants three months after baseline assessment, at the midpoint of the study. The trial flowchart with time-frames is shown in Fig. 1.

**Fig. 1 Fig1:**
[figure not shown]
Flow diagram of participant progress through study

### Ethical considerations

Full ethics approval has been obtained from the Social and Behavioural Research Ethics Committee at Flinders University of South Australia.

### Recruitment of eligible participants

One hundred and fifty mothers (“index mothers”) representing three ethnic groups, Anglo-Australian, Italian-Australian, and Vietnamese-Australian, will be targeted for the first stage of recruitment, based on the following selection criteria: having at least one child aged 10–18 living at home who could participate in the study; and having a minimum of four additional family members (including their child), that span three generations who are living in Australia and who would be eligible to participate in the study. Recruitment will occur by means of advertisement in ethnically targeted areas of the city, via assistance from key community members and organizations, and from invitation letters sent home with children at targeted schools. Interested potential participants will contact the research team who will then ascertain the family’s eligibility to participate by conducting a short eligibility survey via telephone. Interested participants will also be asked to identify their ethnicity and the country of birth of their parents. Families will be categorized into Anglo-Australian, Italian-Australian or Vietnamese-Australian cultural groups based on the birth country of the index participant and their parents, as well as the ethnicity that the family reports to identify with.

Once eligible index mothers and their families are identified, children will be recruited into the study (based on parental consent), and multiple attempts will be made to enrol at least three additional family members based on the index mother’s referral. Families who do not identify with the cultural eligibility criteria or who only have interested participants spanning two generations or less than five members will be deemed ineligible.

All recruited families will receive reimbursement for their time and inconvenience with $50 given to each family after return of all baseline survey data and a further $50 per family after receipt of endpoint survey data. The $50 will be presented each time in the form of five $10 shopping vouchers, one for each participating family member.

### Randomisation

Within each ethnic group, each family will be randomised to either the intervention or control condition upon entering the study. A simple randomisation table will be created pre-trial using Microsoft Excel. Each family that enters the study will be allocated the next available randomised condition provided on the list.

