#### Family health history intervention

Three months after an intervention family has provided the last baseline survey they will receive a health education booklet, entitled ‘Families SHARE’. This will contain a visual family pedigree of the previously identified first and second degree relatives of the index parents with disease markers highlighted for heart disease, diabetes, breast and colorectal cancer. The ‘Families SHARE’ booklet contains a clear description of a family pedigree with guidance to help participants interpret their own and other family members’ risk for disease using the pedigree. In addition, the booklet contains information about genetic and environmental risk for disease along with behavioral and screening recommendations.

The control group of families will receive nothing between baseline and follow-up, and will receive their ‘Families SHARE’ booklet containing their family’s health history upon completion of the study.

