### Time plan

Participant recruitment will be ‘rolling’, as families enter the study they will commence baseline and their own 6-month time-frame.

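### Families are allocated on entry, before baseline is complete, although the workbook goes out only three months after the last baseline survey: an avoidable risk

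*Protocol article*

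**What the plan says.** The Randomisation section of the protocol article sets the time and the method: "Within each ethnic group, each family will be randomised to either the intervention or control condition upon entering the study". On the list it says: "A simple randomisation table will be created pre-trial using Microsoft Excel". On its use: "Each family that enters the study will be allocated the next available randomised condition provided on the list".

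The Time plan ties entry to the start of baseline: "as families enter the study they will commence baseline and their own 6-month time-frame".

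Recruitment of eligible participants describes a staged process: the index mother, then her child, then further relatives, for whom "multiple attempts will be made to enrol at least three additional family members based on the index mother’s referral". Families with fewer than five interested members, or with only two generations, are ineligible.

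The unit is named in two ways. Study design says "mothers from Anglo-Australian, Italian-Australian and Vietnamese-Australian ethnic background will be randomly assigned to an intervention", while Randomisation and the Abstract assign families.

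Delivery comes much later. Family health history intervention says: "Three months after an intervention family has provided the last baseline survey they will receive a health education booklet". Study design likewise puts mailing three months after baseline. Controls receive nothing until the study ends.

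**The concern.** In a cluster trial, the safest point for allocation is after the members of the cluster are known and their baseline data are in. Here the rule puts it at the start of baseline. What follows allocation is mostly self-reported, and some of it is gathered by staff over the telephone.

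Two things are at stake. First, a family that enters but never completes baseline has already been randomised. It is a post-randomisation loss with no baseline data to support an adjustment. Second, if a family or a member of staff learns the arm during this period, it could affect who takes part, how intentions are reported, how fully the family history is given, and how the network interview goes. Those data supply a covariate of the primary model, the family-risk moderator and the baseline of the network comparison.

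Both risks come from a timing rule that the schedule does not need.

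**Working it through.** **1. Order of events, from the article's own sections**

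| Step | Timing | Section |
|---|---|---|
| Allocation from the list | On entry | Randomisation |
| Baseline begins | On entry | Time plan |
| All members' surveys; parents' family health history | During baseline | Baseline survey |
| Network telephone interviews arranged with each member | About 2 weeks after the family's last survey | Family social network survey |
| Workbook mailed (intervention arm) | 3 months after the family's last survey | Family health history intervention |

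Allocation therefore precedes completion of every baseline measure.

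**2. What those measures are used for**
- Baseline intentions are a level 1 covariate (Sample size).
- The family history supplies the pedigree, and with it the average or above-average risk feedback that is a planned moderator (Outcome measures; Primary outcomes).
- The first network interview is the baseline for the comparison of network change between arms (Outcome measures; Secondary outcomes).

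**3. Is there room to allocate later?** Three months is about 13 weeks. The network interviews start about 2 weeks after the last survey, which leaves 13 − 2 = 11 weeks. The interviews with every member and the preparation of the pedigree must fit into those weeks. Later allocation is feasible, but the whole three months is not free.

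**4. Does later allocation cost sample size?** The plan's figure comes first. Inputs from Sample size: f = 0.25, alpha 0.05, power 0.80, 132 families needed, 150 recruited. Two equal arms and a two-sided test are assumed, with the family as the unit.
- Power = P[F(1, N − 2; λ) > F₀.₉₅(1, N − 2)], with λ = N·f².
- The smallest N with power of at least 0.80 is 128. The normal approximation gives 63 per arm, or 126.
- Equal cells in a 2 × 3 layout (arm by ethnic group): 128/6 = 21.3, rounded up to 22, and 22 × 6 = 132. This rounding is inferred; the article says only that the figure is conservative.
- N = 132: λ = 8.25, power 0.813. N = 150: λ = 9.375, power 0.860.

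The time of allocation does not enter this calculation, so 132 and 150 stand.

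**5. What early allocation could cost**
- *Loss.* The allowance is 1 − 132/150 = 12%. Power is 0.813 at 12% loss, 0.798 at 15% (127 families) and 0.775 at 20% (120 families). Loss between entry and the end of baseline uses up this allowance.
- *Differential loss: an illustration on assumptions that are not in the document.* Half of families are less motivated and differ from the rest by D = 0.3 to 0.8 SD on the outcome. The control arm loses an extra share q = 5% to 20% of them before baseline. Bias = D × [0.5/(0.5 + 0.5(1 − q)) − 0.5].
  - Low end: 0.3 × (0.5128 − 0.5) = 0.004 SD.
  - High end: 0.8 × (0.5556 − 0.5) = 0.044 SD.
  - With 66 families per arm, SE = √(2/66) = 0.174 SD, and the type I error is 0.050 to 0.057.
  - This covers differential loss only. It says nothing about distorted baseline answers.

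**6. The simple list within ethnic group**
- With 50 families in a group and X ~ Bin(50, 0.5), the chance of a 20/30 split or worse is 2·P(X ≤ 20) = 0.203.
- For at least one of three groups it is 1 − (1 − 0.203)³ = 0.493.
- Variance factor at 20/30: 1/20 + 1/30 = 0.0833. At 25/25: 2/25 = 0.0800. The ratio is 1.042, so about 4% more variance, or 2% more standard error, within that group.

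**The case against.** **Order relative to relatives' enrolment.** A reader might infer that families are allocated before relatives are enrolled, so that the five-member rule removes families after randomisation. The staged recruitment and the Study design sentence about mothers allow that reading. They do not establish it. The Abstract and Randomisation speak of each family, and the eligibility rule fits a family that enters only once assembled. This objection stands: the order is undefined, not shown to be wrong.

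**Bias needs a known arm.** A reader might also infer that early allocation creates selection bias. Fixing an arm early does no such harm unless the arm is known or foreseeable, and nothing says that recruiters or families learn it. Who holds the list, and how it is concealed, is detail that an article may leave to the full protocol. The surveys are on paper or online, which limits staff influence, and controls receive the booklet in the end, which weakens a reason to decline. This stands too, and it turns the claim into one of avoidable risk. It does not answer loss before baseline, which needs no knowledge of the arm to become a post-randomisation loss.

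**Balance within ethnic groups.** The 20% and 49% chances might suggest that the stratification is pointless or that the ethnic comparison is seriously weakened. At the 20/30 threshold the variance cost is about 4%, ethnic group is in the model, and simple randomisation is valid and hard to predict. In a condensed article, the word simple may not even exclude a restriction. Balance is therefore a side issue.

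**Conclusion.** The point holds as a matter of timing and should be fixed. The article sets allocation at entry and starts baseline at entry, so the arm is fixed before any family's baseline data are complete. Mailing follows three months after the last baseline survey, so the schedule gives no reason for this. That conclusion rests on explicit text and is the same whether entry means the mother or the assembled family.

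The risk to recruitment of relatives depends on how entry is defined. The risk to participation and baseline data depends on the arm becoming known. The document settles neither, so the direction and size of any real bias cannot be stated; the 0.004 to 0.044 SD range rests wholly on assumed inputs. The document does not support a claim that the results will be biased. It supports a claim that a safeguard is available without added families, visits or loss of power, and is not taken.

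**What to change.** - Define entry to the study, and name the family as the unit assigned in both Study design and Randomisation.
- Randomise each family, with concealment, only after the five-member and three-generation requirements are confirmed and its baseline surveys, family health history and baseline network interviews are complete. Do this before the workbook is prepared and mailed. Have the allocation released by someone not involved in recruitment.
- Report families that withdraw before that point as not randomised.
- Optional and minor: use permuted blocks of varied size within each ethnic group.

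Cost: a change of timing and, if blocks are used, a new list. No added visits or data are needed, and the figures of 132 families required and 150 recruited stay as they are. The network interviews and pedigree preparation must be scheduled within the roughly 11 weeks between the start of those interviews and mailing.
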